## Abstract

**Background:**

*Intermittent fasting* is a time-restricted feeding strategy with proven health benefits, which is based on multiple metabolic and endocrine changes, in several patient populations and healthy participants. In the pediatric intensive care unit (PICU), artificial feeding is usually administered 24 hours a day, although solid evidence supporting this practice is lacking. This discards the potential benefits of fasting in this population. We hypothesize that intermittent nutrition with a focus on an overnight feeding interruption (*intermittent fasting*), as compared with 24-hour continuous nutrition, is a feasible and safe strategy, with potential benefits, for critically ill children.

**Objective:**

The aim of the Continuous versus Intermittent Nutrition in Pediatric Intensive Care randomized controlled trial (RCT) is to investigate a strategy of intermittent nutrition with a focus on an overnight feeding interruption period versus 24-hour nutrition during the first 14 days in the PICU.

**Methods:**

The *Continuous versus Intermittent Nutrition in Pediatric Intensive Care* study is an investigator-initiated RCT in a tertiary referral PICU. Critically ill children (term newborn to 18 years), expected to stay in the PICU for ≥48 hours, and dependent on artificial nutrition, are eligible for inclusion. This study will randomize critically ill children (n=140) to a *continuous* versus *intermittent* nutrition strategy. In both groups, similar daily caloric targets will be prescribed. In the *continuous* group (control), nutrition will be administered 24 hours a day, with a maximum interruption period of 2 hours. In the *intermittent* group (intervention), nutrition will be interrupted during an age-dependent overnight fasting period. The study intervention will last until admission day 14, initiation of oral intake, or discharge from the PICU, whichever comes first. The primary outcome is the difference in ketosis between the groups under the condition of noninferiority regarding caloric intake. Secondary outcomes are feeding intolerance; the proportion of severe and resistant hypoglycemic events and severe gastrointestinal complications; and additional observed effects on nutritional intake, circadian rhythm, and clinically relevant outcome measures of the intermittent feeding strategy compared with continuous nutrition.

**Results:**

The study was approved by the Dutch national ethical review board in February 2020. The first patient was enrolled on May 19, 2020. By May 2022, a total of 132 patients had been included in the study. Recruitment of the last patient is expected in Q3 2022.

**Conclusions:**

Although *intermittent fasting* has been proven to have many health benefits in both animal and human studies, the feasibility and safety of this strategy in a PICU setting must be investigated. This RCT will help physicians gain more insight into the feasibility, safety, and potential clinical effects of intermittent feeding with overnight fasting in critically ill children.

**Trial Registration:**

Netherlands Trial Register NL7877; https://trialsearch.who.int/Trial2.aspx?TrialID=NL7877

**International Registered Report Identifier (IRRID):**

DERR1-10.2196/36229

## Introduction

### Nutritional Support for Children in Intensive Care

For a long time, observational studies have suggested that a substantial proportion of critically ill children, most notably infants, develop a pronounced caloric deficit, which has been associated with adverse outcomes [1-4]. This led to recommendations to provide early artificial nutrition via the enteral or parenteral route, targeting to cover at least the calculated or measured resting energy expenditure (REE), compensate for negative protein balance in critical illness, attenuate catabolism, and avoid, possible lethal, complications [5]. To be able to reach caloric targets early in this patient category that is frequently perceived as intolerant to enteral feeding, continuous 24-hour feeding has become a preferable strategy [6].

However, recently, the focus on high macronutrient intake in the acute phase of critical illness has been reconsidered. *The Pediatric Early versus Late Parenteral Nutrition in the Intensive Care Unit (PEPaNIC) randomized controlled trial (RCT)* revealed the beneficial effects of withholding parenteral nutrition (PN) and accepting a macronutrient deficit during the first week of critical illness, such as a decrease in the incidence of new infections, a shortening of the length of stay in the pediatric intensive care unit (PICU) and in the hospital, and a reduction in health care costs [7-9]. This strategy of accepting relative underfeeding of macronutrients in the first week of critical illness has even been shown to be beneficial in patients who are most vulnerable to low nutritional intakes, such as patients who are undernourished and term neonates [10,11]. Withholding PN had no negative effect on participants’ anthropometric measurements during their PICU stay. Moreover, it did not negatively affect their long-term health but actually improved certain parts of their neurocognitive outcome 2 and 4 years later [12,13]. These counterintuitive findings of the beneficial impact of low macronutrient intake during the first week of critical illness were at least partially explained by a fasting response, as observed with increased ketogenesis [14].

### Intermittent Fasting During Pediatric Critical Illness

Owing to the *Pediatric Early versus Late Parenteral Nutrition in the Intensive Care Unit* trial, the potential benefit of macronutrient restriction, or a fasting response, during the first week of critical illness is more recognized. However, knowledge on when safe fasting ends and potentially detrimental effects of starvation start, is lacking. An alternative *fasting mimicking* strategy could be an intermittent feeding pattern, in which a daily fasting response is induced while still providing sufficient amounts of nutrients. *Intermittent fasting* has been widely studied, and the observed health effects of these intermittent feeding strategies are based on changes in metabolic, endocrine, and epigenetic pathways that are also crucial in critical illness [15].

### Aims

Although evenly distributing the daily caloric intake over 24 hours has long been perceived to be more feasible than intermittent feeding in critically ill children, hard evidence for the superiority of continuous feeding over intermittent fasting is lacking [5]. All of the available studies on intermittent feeding in critically ill children examined bolus feeding, and none of those examined the potential of overnight fasting [15]. Currently, no data are available on when the fasting response in critically ill children commences. Furthermore, the severity of illness and nutritional status of the child probably affect the dynamics of a fasting response [15]. Therefore, a study examining the fasting response and potential impact of overnight fasting in critically ill children is warranted. Therefore, the aim of the *Continuous versus Intermittent Nutrition in Pediatric Intensive Care* (ContInNuPIC) RCT is to investigate a strategy of intermittent nutrition with a focus on an overnight feeding interruption period versus 24-hour nutrition during the first 14 days in the PICU.

## Methods

### Ethics Approval and Informed Consent Procedure

The protocol and informed consent forms were approved by the Dutch national ethical review board *Centrale Commissie Mensgebonden Onderzoek* (CCMO; NL72302.000.19). The monitor verifies that the trial will be performed in accordance with the protocol described in the European Medicine Agency’s *Note for guidance on good clinical practice CPMP/ICH/135/95* and the *Declaration of Helsinki*. Eligible patients and, if applicable, their parents or legal guardians, will be informed by one of the members of the research team orally in plain language and in writing. This member of the research team will not be involved in the treatment of the patient. Informed consent will be provided in writing by the parents or legal guardians and confirmed by the child if they are aged ≥12 years. Patients aged ≥16 years will be asked for consent if possible; otherwise, parents or legal guardians will act as legal representatives. For planned admissions, informed consent will be obtained before surgery if possible. For unplanned admissions (or patients with planned admissions whose consent could not be obtained before surgery), informed consent will be obtained within 24 hours after becoming eligible for the study.

### Patients’ Eligibility

#### Inclusion Criteria

Upon admission to the PICU, all the children will be screened for eligibility for inclusion in the ContInNuPIC clinical study. All patients identified by the research team will be logged.

Critically ill children, term newborn to aged 18 years, who are likely to stay in the PICU for >48 hours and to be dependent on artificial nutrition, are eligible for inclusion.

Patients will be considered critically ill if they meet at least one of the following criteria:

Respiratory support (excluding low flow nasal cannula)Hemodynamic support (pharmacological or mechanical)Continuous renal replacement therapy on account of acute renal failure

Patients already on home respiratory support will be considered critically ill only if they have significantly deteriorated compared with normal functioning; that is, need for an increase in the level of support (eg, higher pressure rates, higher fraction of inspired oxygen, or need for hemodynamic support).

#### Exclusion Criteria

Patients fulfilling ≥1 of the following criteria will be excluded:

Preterm neonates (<37 weeks postmenstrual age [PMA] upon admission to the PICU)*Do not resuscitate* code at the time of PICU admissionExpected death within 24 hoursReadmission to the PICU >48 hours after already having been included in the ContInNuPIC trialTransfer from another PICU or neonatal intensive care unit (ICU) after a stay of ≥3 days or having received artificial nutrition (any PN or enteral nutrition [EN] with a caloric intake >10% of predicted REE per day)Ketoacidotic or hyperosmolar comaMetabolic diseases requiring a specific diet or with a contraindication to (intermittent) feedingShort bowel syndrome or other conditions requiring PN before admissionParticipation in another RCT in the PICU with an intervention that might influence the clinical outcome

### Data Collection at Study Entry

At baseline, data on demographic (age, sex, race, ethnicity, and preadmission body weight, and height) and clinical characteristics of the patients will be obtained. For all patients, risk of mortality scores (*Pediatric Index of Mortality score*) [16], disease severity scores (*Pediatric Logistic Organ Dysfunction score*) [17], and the nutritional risk score (*Screening Tool for Risk on Nutritional status and Growth score*) [18] will be calculated, and the *Risk-Adjustment in Congenital Heart Surgery* classification [19] for patients of cardiac surgery will be recorded. In addition, comorbidities, such as the presence of a congenital disease or syndrome, gestational age at birth, presence or history of cancer, diabetes mellitus, kidney disease, liver disease, chronic heart disease, home ventilatory support, and sepsis upon admission, will be noted. In addition, for all patients, baseline results of routine clinical chemistry will be recorded.

### Randomization Procedure

Randomization of participants to *continuous* or *intermittent* nutrition groups will be performed using the ALEA randomization tool (ALEA Clinical, FormsVision), a dedicated computerized system accessible 24 hours a day and 7 days a week. The computer algorithm allocates every consecutive eligible patient to 1 of the 2 treatment arms in a one-to-one allocation ratio using permuted blocks of 10. Patients will be stratified into 3 age groups: neonates (≤44 weeks PMA), infants (<1 year), and children (≥1 year).

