### Blinding

It was considered not feasible to blind treating physicians and patients for the allocated treatment during the time window of the randomized intervention. All outcome assessors and investigators not directly involved in patient care, such as statisticians and laboratory personnel, will be fully blinded to the treatment allocation.

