### Nutritional Support

#### Caloric Intake

During the study, nutritional intake will be provided to both allocation groups according to the current pediatric critical care nutrition guidelines [5,20,21]. In all patients from both study arms, EN will be started as soon as possible (<24 hours), provided that they are hemodynamically stable and without formal contraindications. EN will be administered through a gastric or postpyloric tube and gradually increased using a stepwise protocol (Figure 1), guided by the clinical judgment of the responsible clinician. Caloric goals will be calculated upon admission according to the body weight–based or body weight and length–based Schofield equation for the estimation of REE [22]. In line with the international nutritional guidelines for critically ill children, caloric intake is targeted to reach 1×REE at the end of the first week [5]. After 1 week, caloric target intake increases further to a maximum caloric intake of 1.3×REE for older children and adolescents and up to 2×REE for neonates and infants [20]. The research team will provide nutritional advice based on the standard protocol on a daily basis. The responsible clinician will decide the actual amount of nutrition prescribed based on the protocol, the nutritional intake the day before, and the tolerance of the administered nutrition. If EN cannot be started or increased according to the protocol, the reasons will be recorded in the database.

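### One constant block size of 10 within age strata, in a single-centre open-label trial, makes some late-block assignments foreseeable to anyone who knows the size and tracks the sequence

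*Protocol article*

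**What the plan says.** Under Randomization Procedure, allocation is made by "a dedicated computerized system accessible 24 hours a day and 7 days a week". The algorithm "allocates every consecutive eligible patient to 1 of the 2 treatment arms in a one-to-one allocation ratio using permuted blocks of 10", stratified by three age groups (neonates, infants, older children). One block size is given, and no variation of it is described.

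The Abstract and the Hypothesis section of the Discussion describe a single tertiary PICU. Under Blinding: "It was considered not feasible to blind treating physicians and patients for the allocated treatment during the time window of the randomized intervention". The same section blinds outcome assessors and investigators outside direct patient care, with statisticians and laboratory staff as examples.

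The research team has several roles:
- It identifies and logs patients (Inclusion Criteria) and informs families, through a member not treating that patient (Ethics Approval and Informed Consent Procedure).
- It follows all included patients daily (Protocol Adherence).
- It advises on feeding: "The research team will provide nutritional advice based on the standard protocol on a daily basis" (Caloric Intake).
- It is responsible for daily follow-up of screening, inclusion and protocol compliance (Trial Organization).

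Eligible are critically ill children "who are likely to stay in the PICU for >48 hours and to be dependent on artificial nutrition". For unplanned admissions, consent is obtained within 24 hours of becoming eligible. By May 12, 2022, 132 patients had been included (Results).

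**The concern.** In a permuted block of known size, the assignments already made constrain those still to come. Once one arm has used its five places, every remaining assignment in that block is determined. Here each stratum is identifiable from age, there is only one site's sequence to follow, and an overnight feeding stop of 8 to 12 hours reveals the arm of each enrolled child. The team that finds and approaches new patients also sees enrolled patients daily.

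Foresight matters only when joined to discretion. Judging whether a child is likely to stay beyond 48 hours, or to depend on artificial nutrition, leaves some. The ethics board asked for an overnight glucose infusion in younger intervention patients because of safety concerns (Blood Glucose Management), so reluctance to enrol a fragile child when the intermittent arm is next is conceivable. Selection of that kind could distort the comparisons of ketones, caloric intake and severe hypoglycemia. Adjustment for baseline risk is planned only as a secondary analysis and cannot reach unmeasured traits.

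**Working it through.** **The plan's own figure.** The article gives no figure for predictability. The only figure needed is N = 140, which reproduces: a ketone difference of 0.10 mmol/L with SD 0.16, two-sided 5% and 90% power needs 54 per arm, or 108 in total, and 108 × 1.3 = 140.4.

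**Inputs.** Block size B = 10, so m = 5 per arm; 1:1 ratio; three strata (Randomization Procedure). Stratum sizes are not given; 47 per stratum (140/3, rounded) is an assumption. The observer is assumed to know the block size and all earlier assignments in the stratum.

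**Certain assignments per complete block.** The assignment after k earlier ones is certain if one arm has used all five places, which has probability 2 × C(k,5)/C(10,5), with C(10,5) = 252.

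| Position in block | Probability of being certain |
|---|---|
| 1 to 5 | 0 |
| 6 | 2 × 1/252 = 0.008 |
| 7 | 2 × 6/252 = 0.048 |
| 8 | 2 × 21/252 = 0.167 |
| 9 | 2 × 56/252 = 0.444 |
| 10 | 2 × 126/252 = 1 |

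The sum is 1.667, which agrees with B/(m + 1) = 10/6. This is 16.7% of assignments, and 140 × 0.1667 = 23.3.

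**Incomplete last blocks.** With 47 per stratum there are four full blocks and seven places of a fifth: 4 × 1.667 + 0.008 + 0.048 = 6.72, and 6.72/47 = 14.3%, or about 20 of 140.

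**Best guess.** Always guessing the arm that is behind is right with probability [m + (2^B/C(B,m) − 1)/2]/B = [5 + (1024/252 − 1)/2]/10 = 65.3%, against 50% by chance.

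**Other fixed sizes.** A fixed block of 4 gives 33.3% certain and 70.8% guessed correctly; a fixed block of 6 gives 25.0% and 68.3%. Ten is already a long block.

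**Varying sizes.** Simulation with 47 per stratum and 3,000 runs; the guesser knows the set of sizes but not the size of each block:

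| Block sizes | Certain | Best guess correct |
|---|---|---|
| 10 (fixed) | 14.4% | 64.2% |
| 8/10/12 | 1.5% | 64.6% |
| 6/8/10 | 1.6% | 65.9% |
| 4/6/8 | 2.3% | 67.5% |

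Varying the size removes nearly all certainty but does not lower the best-guess rate, and short mixes raise it.

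**Could a child be deferred past an unwanted slot?** From May 19, 2020 to May 12, 2022 is 723 days, and 132/723 = 0.18 inclusions per day, or 0.06 per stratum if strata are equal. Taking inclusions as a Poisson process, the chance that another inclusion in the same stratum uses the slot within 24 hours is 1 − exp(−0.061) = 6%. With every patient in one stratum it would be 1 − exp(−0.183) = 17%. Deferral would therefore rarely change the arm; declining the child is the route that remains.

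**The case against.** The strongest reply is that the harm depends on facts the article does not give. A reader might infer that recruiters saw every allocation and foresaw the next one. The documents do not establish this. The member who informs a family does not treat that patient, investigators outside patient care are blinded, and nothing says who operates the randomisation system or who knew the block size. A condensed article may leave the withholding of block sizes to the full protocol. This reply stands as a limit on the claim. It does not remove the concern, because the separation covers the patient being approached and not the earlier allocations, and the blinded groups given as examples are not the recruiting team.

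A reader might also infer that publishing the size compromised the trial. With 132 of 140 included, publication could touch at most 8 assignments (8/140 = 5.7%).

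Nor is the allocation list itself exposed. Central computerised allocation conceals it, and the weakness is prediction from past assignments only.

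Finally, declining eligible children would leave a trace, since all identified patients are logged, and secondary analyses adjust for severity of illness and nutritional risk. Both are partial safeguards: the log helps only if it is examined, and adjustment covers measured traits only.

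**Conclusion.** The point holds as a minor to moderate design weakness. With a constant block of 10 in three identifiable strata at one open-label centre, 16.7% of assignments in complete blocks, or about 14% with an assumed 47 per stratum (roughly 20 to 23 of 140), are predictable with certainty, none of them in the first five places of a block. These figures are ceilings: they require a known block size and full tracking of each stratum, neither of which the article states. Together with judgement-based eligibility this could permit selective enrolment, chiefly by declining a child.

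It would go too far to conclude that the comparisons are biased. The article contains no evidence of selective enrolment, and none of its stated figures is wrong on this account.

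**What to change.** **For patients not yet randomised, and for the larger trial foreseen under Strengths and Limitations:** set the randomisation system to randomly varying long blocks, for example 8, 10 and 12, within the age strata. Withhold the sizes from everyone who screens, obtains consent or advises on feeding. Avoid short mixes. The cost is a system setting and a slightly larger possible imbalance per stratum, at most 6 (half of 12) instead of 5 (half of 10). At most 8 assignments in the present trial can benefit.

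**For the present trial, the main step is reporting:**
- State who knew the block size, who entered patients into the system, and whether those people saw earlier allocations.
- Compare the baseline mortality, organ-dysfunction and nutritional-risk scores, already collected under Data Collection at Study Entry, between arms among assignments that were foreseeable from the stratum's history, and set this beside the same comparison in the rest.
- Report eligible children who were not randomised, with reasons, from the screening log.

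The baseline check uses existing data but is coarse. With about 20 foreseeable assignments, or about 10 per arm, the 95% interval for a standardised difference has a half-width of about 1.96 × √(2/10) = 0.88 SD. It can show gross selection but cannot rule out moderate selection, so it should be presented descriptively.

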### Blinding

It was considered not feasible to blind treating physicians and patients for the allocated treatment during the time window of the randomized intervention. All outcome assessors and investigators not directly involved in patient care, such as statisticians and laboratory personnel, will be fully blinded to the treatment allocation.

### Protocol Adherence

The medical and nursing staff of the PICU were informed and trained extensively during regular meetings before the start of the trial and were familiarized with the protocol. To optimize protocol compliance, reminders for study interventions and measurements will be incorporated into the electronic patient data management system. Moreover, the research team will provide a daily follow-up of all included patients.

### Nutritional Support

#### Caloric Intake

During the study, nutritional intake will be provided to both allocation groups according to the current pediatric critical care nutrition guidelines [5,20,21]. In all patients from both study arms, EN will be started as soon as possible (<24 hours), provided that they are hemodynamically stable and without formal contraindications. EN will be administered through a gastric or postpyloric tube and gradually increased using a stepwise protocol (Figure 1), guided by the clinical judgment of the responsible clinician. Caloric goals will be calculated upon admission according to the body weight–based or body weight and length–based Schofield equation for the estimation of REE [22]. In line with the international nutritional guidelines for critically ill children, caloric intake is targeted to reach 1×REE at the end of the first week [5]. After 1 week, caloric target intake increases further to a maximum caloric intake of 1.3×REE for older children and adolescents and up to 2×REE for neonates and infants [20]. The research team will provide nutritional advice based on the standard protocol on a daily basis. The responsible clinician will decide the actual amount of nutrition prescribed based on the protocol, the nutritional intake the day before, and the tolerance of the administered nutrition. If EN cannot be started or increased according to the protocol, the reasons will be recorded in the database.

